# Introduction

Polypharmacy and the prescribing of inappropriate medication is a common problem in the USA as well as in Europe. Particularly older people are at higher risk for inappropriate medication and consequently for drug related complications (Fick DM, 2008). An increased number of comorbid conditions in the higher aged and therefore a greater number of physicians involved in the care of the elderly put them at higher exposure for polypharmacy and accordingly for inappropriate medication (Gokula M, 2012; Fialová D, 2005). There are at least six major consequences of polypharmacy: nonadherence, adverse drug reactions, drug-drug interactions, increased risk of hospitalisation, medication errors and increased costs (Rollason V, 2003). Studies show a correlation between receiving inappropriate medication and increased morbidity and mortality (Lau D, 2005; Fick DM, 2008). In addition, physiologic changes and impaired organ functions with increasing age lead to altered pharmacokinetics and pharmacodynamics (Beglinger C, 2008; Page RL, 2010). The prescription of the appropriate medication for elderly patients is therefore a challenge for clinicians. The prevalence of polypharmacy and inappropriate medication in Europe is alarming. Fifty-one percent of the elderly in Europe take 6 or more medications and almost 20% of patients use at least one inappropriate medication (Fialová D, 2005). Only few data are available on the situation in Switzerland. A recent prospective European study showed that the prevalence of potentially inappropriate medicines used by patients ≥ 65 years admitted with acute illness to the acute geriatric medicine unit at the Geneva University Hospital was 77.3% (according to STOPP criteria). This was the highest prevalence among the 6 participating European centers (Gallagher P, 2011).

Many interventions aiming at reliably reducing the number of inappropriate medications in elderly patients and at improving the patient’s safety have been studied. Such interventions include for example medication review by multidisciplinary teams or complex multifaceted pharmaceutical care intervention (medication review, consultation, team participation) (Gokula M, 2012; Patterson SM, 2012; Steinman MA, 2010; Topinková E, 2012). Most of these strategies are efficacious for reducing polypharmacy, but are very complex and time-consuming and therefore not easily applicable in the busy clinical daily routine (Gokula M, 2012; Spinewine A, 2007). User-friendly screening tools which can assess the appropriateness of prescribing and do not need a multidisciplinary team do exist. One of the most frequently used is the Beers’ Criteria list, consisting of a list of drugs to avoid in elderly people (Fick DM, 2003). However, most of these tools based on explicit criteria, including the Beers’ Criteria, were developed in the USA or Canada and are hardly applicable in Europe because of the differences in populations, national drug formularies and prescribing attitudes. For example, almost half of the drugs listed in Beers’ criteria are unavailable in European countries (Fialová D, 2005; Gallagher P, 2011). Moreover, explicit (criterion-based) indicators of appropriateness of prescribing are usually drug-oriented or disease-oriented and do not address for example the burden of comorbid disease in the individual patient (Spinewine A, 2007). A research group in Ireland validated a new set of explicit criteria for potentially inappropriate medication use in older adults called STOPP (Screening Tool of Older Person’s Prescriptions) and START (Screening Tool to Alert doctors to Right Treatment) (Gallagher P, 2008). These authors showed also that potentially inappropriate medicines (PIMs) identified according to STOPP criteria and prescribed to patients 65 years or older are significantly associated with avoidable adverse drug events (Hamilton H, 2011). With other tools (implicit approaches) clinicians use information from the patient and published work (instead e.g. of a fixed list of to-avoid-drugs) to make judgements about appropriateness. They address multiple elements of medication prescribing, which are relevant for many different drugs, clinical conditions and settings (Hanlon JT, 1992). These implicit (judgement-based) approaches are flexible, focus on the patient, rather than on drugs or diseases, and are potentially the most sensitive, but they are time-consuming and depend on the user’s knowledge and experience (Hanlon JT, 1992; Spinewine A, 2007).

It is difficult to design an adequate tool which is applicable in the busy clinical routine, respects the complexity and context of the patient and is not limited to a specific region or prescribing habits. We tried to develop such a tool with the aim to improve the appropriateness of prescribing and reduce polypharmacy in an internal medicine unit of a university-affiliated community hospital. We developed a simple checklist which is based on two frameworks proposed in the literature and designed to improve the prescribing process in recognition of patient complexity (Scott IA, 2012; Dovjak P, 2012). These frameworks focus on topics like individual drug-related risk, expected life span, care goals, verification of diagnoses, likely time to benefit, and benefit-risk thresholds of individual drugs and their relative utility (Scott IA, 2012). However, they are complex and require a very detailed and time-consuming evaluation of the patient’s situation and context. We simplified these frameworks and tried to adapt them to the daily clinical routine in order to have a simpler tool aimed at supporting the physician in improving prescribing and reducing polypharmacy.

# Objectives

The primary aim of this study among patients aged ≥ 65 years admitted with an acute illness to an internal medicine unit of a community hospital in north western Switzerland is:

1. To assess the efficacy and safety of a simple prescriber checklist for reducing inappropriate prescribing and polypharmacy.

Secondary aims are:

1. To assess the number of prescribed drugs, the prevalence of polypharmacy (concomitant use of ≥ 5 drugs) and hyperpolypharmacy (concomitant use of ≥ 10 drugs).
2. To assess the prevalence of potentially inappropriate medicine use (PIMs; according to STOPP criteria) and of potentially inappropriate prescribing omissions (PPOs; according to START criteria).
3. To assess the prevalence of prescription and the rate of inappropriate prescription of following drugs: non-steroidal anti-inflammatory drugs (NSAID); proton pump inhibitors (PPI); systemic corticosteroids; metamizol-natrium (Novalgin™); potent opiates.

# Methods

1. ***Study design***

Single-center, interventional, quasi-experimental before-after study.

## Study population

Eligible participants are the first 450 consecutive patients aged ≥ 65 years who will be hospitalised on the internal medicine unit of the Kantonsspital Olten from September 1, 2013 to November 30, 2013. The control group consists of the first 450 consecutive patients aged ≥ 65 years hospitalised on the Internal Medicine Unit of the Kantonsspital Olten between September 1, 2012 and November 30, 2012. As residents and fellows rotate on different wards of the Department of Internal Medicine every 1-2 months, randomization of the intervention to different wards was not possible. Therefore, as ≥ 80% of residents and fellows work in the Department of Internal Medicine for ≥ 2 years, we defined as control group elderly patients hospitalised during the same period one year earlier. We choose the same period to take into account differences in polypharmacy resulting from saisonal variability in prescription of drugs. Each patient will be included only once in the study (at the first hospitalisation during the study period. Patients who are hospitalised during the period 2012 and 2013 will not be considered in the study population 2013).

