The medical team on the wards will integrate the use of the described checklist in usual care of all patients hospitalised in the Department of Internal Medicine. The checklist is a tool to improve the application of strategies which are considered standard of care to optimize drug prescriptions and avoid errors or adverse drug events (Scott IA, 2012; Dovjak P, 2012; Meyer-Nikolic VA, 2012).

1. ***Follow-up***

As safety parameter we will assess the all-cause re-hospitalisation rate at 30 days after discharge using administrative data of the hospital. We believe that the re-admission rate calculated only on the basis of re-hospitalisations at the Kantonsspital Olten is representative because the Kantonsspital Olten is the only hospital in the eastern part of the Canton Solothurn and the great majority of patients discharged from the internal medicine unit of the Kantonsspital Olten come back at the same hospital if any new or recurrent problem occur after discharge.

1. ***Data collection***

At the Department of Internal Medicine, Kantonsspital Olten, most patient information (including diagnoses, therapy at admission and discharge, laboratory results, progress notes, etc.) is currently recorded in the electronic patient record. However, some other information, such as one part of the nursing documentation, is still on paper. Data will be collected from the electronic patient records and completed, if necessary, by review of the paper patient records. The medication at admission and discharge of each patient will be reviewed independently by two of the investigators ([name], [name]), who will assess whether the medication is appropriate or inappropriate according to STOPP and START criteria. Discrepancies in this assessment will be resolved by consensus. Following data will be recorded on a standardised case report form: age; gender; place of residence (home or nursing home); number of diagnoses; Charlson Comorbidity Index (Charlson ME, 1987); length of stay; number of medications at admission and discharge; prescription of NSAID, PPI, systemic corticosteroids, metamizol-natrium, potent opiates, at admission and discharge, and whether these prescriptions are appropriate or not; number of potentially inappropriate medicines (PIM) used and number of potentially inappropriate prescribing omissions (PPO), both at admission and discharge; all-cause re-hospitalisation at 30 days.

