Basic demographic characteristics, cumulative co-morbidity (Charlson Co-morbidity Index), the type and number of drugs prescribed and the prevalence of inappropriate prescribing at admission and discharge will be compared using the chi-squared test or Fisher’s exact test for categorical variables, and the Mann-Whitney U test for continuous variables. The results will be analysed with an intention-to-intervention analysis, where all subjects are compared in the intervention group regardless of whether the checklist has been used by the physician in charge. All analyses will be performed using STATA software version 11 for Windows (Stata Corp, College Station, Texas, USA).

1. ***Ethical considerations***

The protocol of the study will be submitted to the local research ethics committee (Kantonale Ethikkommission Aargau / Solothurn). Because the aim of the study is only to evaluate an instrument (the checklist) to improve quality of patient care through better implementation of recognised standards of care (such as medication reconciliation and appropriate prescribing), and data are collected as part of the continuous quality assurance programme of the Kantonsspital Olten, no informed consent from patients will be required.

**Table 1.** Sample size required for each group to detect a 10-20% reduction of the prevalence of inappropriate prescription through a simple checklist according to different power and significance levels.

| Prevalence of polypharmacy or inappropriate drug prescription at admission | Prevalence of polypharmacy or inapproriate drug prescription at discharge | Significance level | Power | Sample size for each group | Total sample size |
| --- | --- | --- | --- | --- | --- |
| 30% | 10% | 0.05 | 90% | 92 | 184 |
| 30% | 20% | 0.05 | 90% | 412 | 824 |
| 20% | 10% | 0.05 | 90% | 286 | 572 |
| 30% | 10% | 0.01 | 90% | 127 | 254 |
| 30% | 20% | 0.01 | 90% | 576 | 1152 |
| 20% | 10% | 0.01 | 90% | 397 | 794 |
| 20% | 10% | 0.01 | 80% | 317 | 634 |

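### One autumn before and one after cannot separate the checklist from a one-year change in discharge prescribing, so the result should not be called efficacy

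*Protocol*

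**What the plan says.** Under Study design the protocol describes a "Single-center, interventional, quasi-experimental before-after study". Under Study population, the control group is the first 450 eligible patients "hospitalised on the Internal Medicine Unit of the Kantonsspital Olten between September 1, 2012 and November 30, 2012", and the intervention group is the first 450 in the same months of 2013. Two reasons are given for this control. Randomising wards was not possible because residents and fellows rotate, while at least 80% of them stay for two years or more; hence "we defined as control group elderly patients hospitalised during the same period one year earlier". The second reason is season: "We choose the same period to take into account differences in polypharmacy resulting from saisonal variability in prescription of drugs".

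The Intervention section gives the checklist to every physician of the department, so 2013 has no unexposed comparison. The Outcomes section places both primary measures at discharge: the proportion of patients with a potentially inappropriate medicine (PIM) and the number of drugs. Statistical methods names chi-squared or Fisher tests and the Mann-Whitney test, with no adjustment. The aim under Objectives is nevertheless causal: "To assess the efficacy and safety of a simple prescriber checklist for reducing inappropriate prescribing and polypharmacy".

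**The concern.** With one block before and one block after, the estimated difference is the checklist effect plus whatever else changed in discharge prescribing over the year. Choosing the same months removes season. Continuity of staff limits change in who prescribes. Neither removes change in how the same doctors prescribe one year later. The tests named cannot detect such a change, and no model added later can recover a trend from two blocks, because the data periods themselves are fixed under Study population.

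Some change is conceivable from the protocol's own text. It describes the checklist as helping to apply "strategies which are considered standard of care to optimize drug prescriptions and avoid errors or adverse drug events", builds it on frameworks published in 2012, and notes that "data are collected as part of the continuous quality assurance programme of the Kantonsspital Olten". A downward drift could be taken for efficacy; an upward drift could mask a true benefit.

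**Working it through.** **The plan's own figure.** Inputs from Sample size: 30% against 20%, significance level 0.05, power 90%. The two-sided formula for two independent proportions with continuity correction gives 412 per group, exactly as stated (392 without the correction). All seven rows of Table 1 reproduce in the same way. The sample size is not in question here.

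**Effect of drift on the PIM comparison.** Inputs: n = 450 per group (protocol); 2012 prevalence 30% (protocol); checklist effect zero (by construction); drift d of 2, 3 or 5 points (assumption, since the protocol gives none). The 2013 prevalence is p2 = p1 − d. With the mean prevalence p̄ = (p1 + p2)/2:

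- SE under the null: s0 = √[2 p̄(1 − p̄)/n]
- SE under the drift: s1 = √[(p1(1 − p1) + p2(1 − p2))/n]
- P(significant) = Φ[(d − 1.96 s0)/s1] + Φ[(−d − 1.96 s0)/s1]

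For d = 5 points: p̄ = 0.275, s0 = 0.02977, s1 = 0.02972. The first term is Φ[(0.05 − 0.05834)/0.02972] = Φ(−0.28) = 0.389, and the second is below 0.001.

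| Drift (assumed) | 30% baseline | 45–60% baseline |
| --- | --- | --- |
| 0 points | 5% | 5% |
| 2 points | 10% | 9% |
| 3 points | 17% | 15% |
| 5 points | 39% | about 33% |

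These are two-sided. At 2 points and a 30% baseline, 9.7% favours the checklist and 0.4% goes the other way; at 5 points essentially all of it favours the checklist.

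**Drift in the other direction.** If the true effect is 10 points from 30%, power with 450 per group is 94%. An upward drift of 3 points leaves an apparent 30% against 23% and power of 66%. A drift of 5 points leaves 30% against 25% and power of 39%.

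**Drug count.** With an assumed SD of 4 drugs, SE = 4 × √(2/450) = 0.27. A drift of 0.3 or 0.5 drugs with no checklist effect gives a significant result 20% or 47% of the time.

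**What a monthly series could add.** Assumptions: SD 4; 150 patients in each of the six study months (450/3); 50 or 150 patients in each added month; linear trend plus a step at September 2013; independent patients. The SE of the step, in drugs, is:

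| Added months | No season term (150 / 50 per month) | With 12-month harmonic (150 / 50 per month) |
| --- | --- | --- |
| December 2012 to August 2013 | 0.29 / 0.41 | 0.48 / 0.67 |
| December 2012 to July 2013 | 0.33 / 0.46 | 0.67 / 0.93 |

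The simple difference has SE 0.27. The second row is the relevant one, because the Intervention section has the checklist presented in August 2013.

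**Why a same-sign rule is not enough.** Under pure linear drift the step has expectation zero, so its sign is close to a coin toss. With a fall of 0.5 drugs and no checklist effect, 47% of studies show a significant simple difference. Asking only that the step point the same way still leaves about 25–27% falsely attributed to the checklist.

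**The case against.** The strongest reply is that exposure to calendar trend is what an uncontrolled before-after study is. The protocol declares that design, explains why wards could not be randomised, and defends its choice of months and staff. All of that stands, and it is why the design itself need not change. It does not support the word efficacy in the aim.

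A second reply is that drug counts and PIMs are recorded and compared at admission as well as at discharge in both years. This is correct and useful. Admission values would show part of any year-to-year change, in pre-admission prescribing and patient mix. They would not show drift in the unit's own discharge habits, and the protocol states no rule for using them to qualify the discharge comparison.

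A third reply is that the evidence for drift is thin. This also stands. The remarks on standard of care and quality assurance are there to justify the intervention and the absence of consent, and a continuous programme could have run equally in both autumns. A reader might infer that prescribing was already improving, or that ordinary drift would be reported as efficacy. The document supports neither: it gives no trend, size or direction, and even at an assumed 5-point drift most studies (61%) would not be significant.

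**Conclusion.** The point holds in limited form. As written, the plan cannot distinguish the checklist from a one-year change in discharge prescribing, so a conclusion of efficacy from this contrast would not be sound. What can be concluded is the change between the two autumns.

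The size of the problem is unknown. The figures of 10%, 17% and 39% rest on assumed drifts of 2, 3 and 5 points and no checklist effect; those for the drug count also rest on an assumed SD of 4. They show what the test would do with a drift, not that one occurred. Nor does the point make the comparison worthless: it remains a valid description of two periods, and the sample size is correct for the stated difference. The study can proceed, but the claim should be brought into line with the design.

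**What to change.** 1. **Reword the claim.** In Objectives and in the planned conclusion, replace efficacy with the change in discharge PIM prevalence and drug count between autumn 2012 and autumn 2013, and state that calendar trend is not excluded. This costs nothing and is the only remedy offered here that fully covers the PIM outcome.
2. **Use the admission data as support.** Report the between-year difference in admission values and the between-year difference in admission-to-discharge change. Say that neither removes drift in the unit's own discharge prescribing. No new data are needed.
3. **Add a monthly series if the record allows.** The Data collection section says "most patient information (including diagnoses, therapy at admission and discharge, laboratory results, progress notes, etc.) is currently recorded in the electronic patient record", and the 2012 control group already depends on past records, although completeness for the months between is not stated. Extract the discharge drug count by month from December 2012 to July 2013, without STOPP/START rating. Leave out August 2013 as a roll-out month. State how repeat patients are counted, because counting each patient once across a longer series could remove frequently readmitted patients from later months and create an artificial trend. Report the segmented-regression step with its 95% confidence interval, with and without a season term, and do not use a same-sign rule.

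The cost of item 3 is one extraction and one analysis. Its downside is precision: on the assumptions above, the SE is about 0.33–0.46 drugs without a season term and 0.67–0.93 with one, against 0.27 for the simple difference. It should therefore be supporting, not primary, and it does not address PIMs.

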Only the investigators will have access to the case report forms, which will be stored in a locked cabinet in the office of the investigators at the Kantonsspital Olten. For statistical analysis data will be anonymised.

1. ***Outcomes***

The primary outcome is the reduction of the proportion of patients using inappropriate drugs (PIM) at discharge and the reduction of the number of prescribed medications at discharge.

Secondary outcomes are:

1. the proportion of patients with potentially inappropriate prescribing omissions (PPOs) at admission and discharge,
2. the prevalence of prescription and the rate of inappropriate prescription of following drugs: non-steroidal anti-inflammatory drugs (NSAID); proton pump inhibitors (PPI); systemic corticosteroids; metamizol-natrium (Novalgin™); potent opiates at admission and discharge,
3. the all-cause rehospitalisation rate at 30 days after discharge

in the intervention and in the control group.

1. ***Sample size***

The sample size is determined by the estimated change in the proportion of users of inappropriate drugs at discharge and the expected size of the intervention effect. Given the high prevalence of polypharmacy in elderly patients (58% in Europe according to Gallagher et al., Gallagher P, 2011) and that 34-77% of these patients use at least one inappropriate drug (PIM), we believe that even a reduction of 10% in patients taking inappropriate medications or a reduction of 10% in the prevalence of polypharmacy will be of clinical relevance. To detect an effect of 10% of the checklist (decrease in prevalence of inappropriate drug prescription and/or polypharmacy from 30% at admission to 20% at discharge) with a probability (power) of 90% at a significance level of 0.05, a sample size of 824 patients (412 in each group) will be needed (table 1.). Therefore, we aim to include 900 patients (450 patients in the intervention group enrolled during the period September-November 2013, and 450 patients in the control group who had been hospitalised in September-November 2012).

1. ***Statistical methods***

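### Patients hospitalised in both the 2012 and the 2013 window are excluded from the intervention cohort only; the controls have no matching one-year look-back, which probably favours the checklist by a small amount

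*Protocol*

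**What the plan says.** Under Methods, Study population, both cohorts are defined as consecutive series from the same three calendar months. For 2013: "Eligible participants are the first 450 consecutive patients aged ≥ 65 years who will be hospitalised on the internal medicine unit". For 2012: "The control group consists of the first 450 consecutive patients aged ≥ 65 years hospitalised on the Internal Medicine Unit".

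The section then adds a once-only rule: "Each patient will be included only once in the study (at the first hospitalisation during the study period". Across the two years this rule is enforced by one exclusion: "Patients who are hospitalised during the period 2012 and 2013 will not be considered in the study population 2013". I read it as covering patients with a stay in both September-November windows. No exclusion is stated for 2012 controls who had a stay in September-November 2011.

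Under Outcomes, the primary outcome has two parts, PIM use at discharge and the number of drugs at discharge: "The primary outcome is the reduction of the proportion of patients using inappropriate drugs (PIM) at discharge". All-cause re-hospitalisation at 30 days is the safety parameter (Follow-up). Statistical methods names chi-squared, Fisher and Mann-Whitney tests. It names no adjusted model.

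**The concern.** The study is a single-centre, unrandomised before-after comparison, so a difference in who may enter each cohort goes straight into the estimated effect. Here one cohort has a one-year look-back and the other has none.

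The patients affected are those with a stay in the same quarter one year before. They are removed from 2013, but their counterparts (2012 patients with a 2011 stay) remain among the controls. The Introduction ties a higher number of comorbid conditions to polypharmacy and inappropriate medication, and lists hospitalisation among the consequences of polypharmacy. By that reasoning these patients probably carry more drugs and more PIMs, and they are probably more likely to be readmitted.

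If so, the intervention cohort would look better at discharge even if the checklist did nothing. The 30-day re-hospitalisation comparison would be tilted in the same direction, which could hide part of any harm. A larger sample does not shrink this kind of error.

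**Working it through.** **The plan's own figure.** For 30% versus 20%, two-sided significance level 0.05 and 90% power, the continuity-corrected two-proportion formula gives 412 per group, as stated under Sample size. Without the correction it gives 392. The protocol does not state sidedness; the two-sided form reproduces all seven rows of Table 1. The planned effect is thus 10 points, with 450 per group intended.

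**Inputs for the bias.**
- Overall PIM prevalence 30%, the starting value in the sample size section.
- 450 per group, from the protocol.
- f, the share of a cohort that also had a stay in the previous year's window: not given, assumed 3%, 5% or 10%.
- q, PIM prevalence in those patients: not given, assumed 40% or 50%.
- No true checklist effect, and f and q alike in both years.

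**Formulas.** The control cohort keeps these patients, so its prevalence is 0.30. The 2013 cohort loses them:

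p₂₀₁₃ = (0.30 − f·q) / (1 − f), and spurious fall d = 0.30 − p₂₀₁₃.

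The two-sided rejection rate uses the pooled two-proportion z-test:

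1 − Φ((1.96·s₀ − d)/s₁) + Φ((−1.96·s₀ − d)/s₁),

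where s₀ is the pooled and s₁ the unpooled standard error.

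**One case in full** (f = 10%, q = 50%): p₂₀₁₃ = (0.30 − 0.05)/0.90 = 0.2778, so d = 0.0222. With s₀ ≈ s₁ ≈ 0.0302, the upper tail is 11.0% and the lower tail 0.4%, together 11.4%.

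| Overlap f | PIM in overlap q | 2013 prevalence | Spurious fall (points) | Two-sided false significance |
| --- | --- | --- | --- | --- |
| 3% | 40% | 29.7% | 0.3 | 5.1% |
| 5% | 40% | 29.5% | 0.5 | 5.3% |
| 10% | 40% | 28.9% | 1.1 | 6.5% |
| 3% | 50% | 29.4% | 0.6 | 5.5% |
| 5% | 50% | 28.9% | 1.1 | 6.4% |
| 10% | 50% | 27.8% | 2.2 | 11.4% |

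**Cross-check.** If g is the excess prevalence over patients without a prior-window stay, the bias is simply f·g. With f = 3-10% and g = 10-20 points this gives 0.03 × 10 = 0.3 to 0.10 × 20 = 2.0 points, in agreement with the table.

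**Other outcomes, also on assumed inputs.** For drug count the bias is f times the excess number of drugs: 5-10% overlap and two extra drugs give 0.1-0.2 drugs. For 30-day re-hospitalisation at 15% overall and 30% in the overlap, (0.15 − f·0.30)/(1 − f) gives a spurious fall of 0.5, 0.8 or 1.7 points at 3%, 5% or 10% overlap.

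**The case against.** Counting each patient once is a legitimate aim, because the named tests assume independent observations. The excluded group is also narrow: a patient must have been on the unit in one quarter, survived, and come back to the same unit in the same quarter a year later. A reader might infer that repeat-admission patients in general leave the intervention group. The text does not support that. Patients readmitted within September-November 2013, or with a stay only between December 2012 and August 2013, remain eligible and are counted once.

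The direction is inferred. The Introduction speaks of comorbidity, polypharmacy and hospitalisation in general, not of PIM use in patients who return after a year. The inference is reasonable, but it is not a documented fact.

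The size rests on assumptions. A reader might also infer a badly inflated error rate: at 15% overlap and 50% PIM in the overlap, the same formula gives a 3.5-point fall and about 22% false significance. Nothing in the protocol supports choosing that corner.

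Finally, drug count, PIM use and the Charlson index are recorded, and the groups are compared at admission as well as at discharge. A sicker control group could therefore be seen before the checklist could act. An analysis plan, if one exists, may add adjustment.

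These arguments limit the scope and size of the problem. They do not remove it. The unequal rule is stated in the text, and seeing an imbalance at admission is not the same as correcting it. Adjustment in the analysis would leave the entry rule unequal.

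**Conclusion.** The point holds as a difference in eligibility between the two cohorts. It probably favours the checklist on PIM prevalence, drug count and 30-day re-hospitalisation. Over the moderate range above, the spurious fall in PIM is about 0.3-2.2 points against the planned 10, and two-sided false significance is about 5.1-11.4% instead of 5%. This rests on a 30% overall prevalence, an overlap of 3-10%, a PIM prevalence of 40-50% in the overlap, and similar overlap and excess in both years. The protocol supplies only the first of these.

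A reader might go further and infer that the rule could by itself produce a positive trial. These figures do not support that: even the largest shift in the table is less than a quarter of the target effect. The rule could enlarge a real effect or tip a borderline result. It should be fixed, since the remedy is cheap, but it does not by itself invalidate the design.

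**What to change.** Apply the same one-year look-back to both cohorts. In Study population, add that patients hospitalised on the unit in September-November 2011 are excluded from the 2012 controls, identified from the hospital's administrative records, and that the next consecutive eligible patients take their place. If overlap and excess are similar in the two years, the expected bias from this source falls to about zero. The sample size calculation does not change.

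The cost is a records check for 2011 and chart review of the replacement controls. Replacement matters: removing 10% of 450 without it would leave 405, below the 412 required. If the 2012 window runs out of eligible patients, the control group may end slightly under 450, which is acceptable down to 412. Results would then apply to patients without a stay in the same window a year earlier, in both groups alike.

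Do not equalise the groups by dropping controls who return in 2013, because that selects controls on a future event.

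As a sensitivity analysis, keep patients seen in both years in both cohorts, at their first stay in each window, with standard errors clustered on patient. This departs from the once-only rule and needs a model that Statistical methods does not name, so it should not be the main remedy. Reporting the number of patients excluded by the look-back in each year would show how much the rule mattered.
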